# Research Questions

- 1. **Research Questions**

Among HIV-infected patients enrolled in HIV care at eight clinics on Mfangano, Remba or Ringiti Islands, Kenya who have missed a HIV clinic appointment by at more than 3 days:

- - 1. Does the Microclinic social network-based HIV intervention reduce gaps in clinical HIV care over 12 months of follow-up, as compared to standard of care?
    2. Does the Microclinic social network-based HIV intervention improve the proportion of time patients spend adhering to recommended clinic appointments over 12 months of follow-up, as compared to standard of care?
    3. Does the Microclinic social network-based HIV intervention reduce time to re-engagement in clinical HIV care, as compared to standard of care?
    4. Does the Microclinic social network-based HIV intervention improve retention in HIV care at 12 months of follow-up, as compared to standard of care?
    5. Does the Microclinic social network-based HIV intervention increase the proportion of patients who are virologically suppressed at 12 months of follow-up, as compared to standard of care?
  1. **Hypotheses**
     1. Participants randomized to the microclinic HIV intervention will have a lower incidence rate of 90-day absence from clinical HIV care over 12 months post-randomization than participants randomized to standard of care.
     2. Participants randomized to the microclinic HIV intervention will spend a larger proprotion of time ‘in care’ than those randomized to standard of care. Time in care is defined as the number of days a patient spends adherent to his or her clinic visit schedule divided by the total number of days the patient is observed. See measurement section below for more detail).
     3. Participants randomized to the microclinic HIV intervention will have a higher hazard of re-engagement in clinical care than those randomized to standard of care. Re-engagement is defined as attending an HIV clinic visit and receiving the patient’s ART prescription from the clinic pharmacy.
     4. A larger proportion of participants randomized to the microclinic HIV intervention will be retained in HIV care at 12 months than those randomized to standard of care. Retention is defined as being alive and not missing a clinic appointment by 90 days or more as of study closure at 12 months post-enrollment of the last study participant.

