### Measurements

The predictor of interest is the baseline treatment assignment, as determined by randomization. All analysis will be conducted using an intention-to-treat analysis.

Covariates of interest will be collected through participant surveys at baseline and study closure, as well as routine clinic data collected at the participant’s original clinic and any other clinics from which he or she receives HIV care during the course of the study. Baseline surveys (Appendix C) will collect data related to the following:

1. Demographic characteristics
2. Contact and locator information
3. HIV-related stigma[23](#_ENREF_23)
4. HIV status disclosure
5. Social support
6. Clinic data (date first HIV positive, date of enrollment)
7. Reason for missed clinic appointment, including name of other facilities where care was received

At the end-of-study survey (Appendix G), additional data will be collected related to possible adverse events that may or may not be related to the intervention. In addition to specific questions in the survey, an open-ended question will be used to assess other adverse experiences related to issues such as stigma, unintended disclosure or poor treatment by health center staff. Participants will be asked whether they attribute any or all of these experiences to participation in the study. Additionally, participants in the intervention arm will specifically be asked about adverse experiences related to group status disclosure, again using both a checklist and an open-ended question. At the end-of-study survey, patients will be asked if they are currently in care and, if so, which clinic. Reasons for transfer or disengagement from the original clinic will be assessed. For patients who were lost-to-follow-up (missed a clinic visit by ≥90 days and did not return to clinic) or who transferred out from their original clinic, a patient tracing survey will also be conducted. (Appendix F) See description of clinic data capture below regarding determination of patient’s visit history and transfer status.

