## Data Analysis

Primary analyses will be conducted using only the index study participants (i.e. participants who are HIV-infected and who missed a clinic visit by >3 days to become eligible for study participation).

Hypothesis 1

We will compare the indicence of 90-day absence from clinical HIV care between study arms using a Cox proportional hazards model. Additionally, we will depict the cumulative incidence of 90-day absence using the Cumulative Incidence Function, with death as a competing event.[24](#_ENREF_24) Primary analysis will be unadjusted, with standard errors adjusted for clustering of participants who are in the same microclinic group. Validity of the proportional hazards assumption will be assessed graphically and through formal testing using Schoenfeld residuals.

Hypothesis 2

‘Time in care’ will be calculated for each participant by subtracting the total days ‘out of care’ from the total length of follow-up and divided by the total length of follow-up. This will constitute a proportion depicting the proportion of time a given participant has spent adhering to his or her clinic appointment schedule. The number of days ‘out of care’ will be calculated by summing the total number of days between missed appointments and next clinic visits for each participant over the course of follow-up. Analysis will be conducted using linear regression to compare the mean proportion of ‘time in care’ between study arms. Standard errors will be adjusted for clustering, as in Hypothesis 1. Bootstrapping with cluster re-sampling will be conducted to address potential non-normality of residuals. Primary analysis will be conducted using unweighted time in care proportions for all participants, with sensitivity analysis conducted where each participant is weighted according to the length of follow-up.

Hypothesis 3

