|  ***Questions C5k is only for deceased patients not yet started on ART at original clinic.*** | | | | | | | | | | | | | | | | | | |
|  C5k. Had he/she started ART somewhere else besides [name of original clinic]? | |  Yes   No**Go to Section E**   Not asked **Go to Section E**   Unknown**Go to Section E** | | C5k(i). When did he/she start ART? | | | | | | - -  DAY(*dd*) MONTH (mmm) YEAR **(yy)** | | | | | | | |  Unknown |

| **SECTION D: TRACKER UNABLE TO COMMUNICATE WITH PATIENT OR INFORMANT** Check local death registry: | | | | | | | |
| --- | --- | --- | --- | --- | --- | --- | --- |
| D1. Is the patient dead? | |  Yes   No evidence of death in registry  (registry consulted)   Unknown (no registry data  available) | |  D1a. When did the patient die? | | | - -  DAY(*dd*) MONTH (mmm) YEAR **(yy)** |
| ** GO TO SECTION E** | | | | | | | |
| **SECTION E: TRANSFER CLINIC DATA** | | | | | | | |
| F1. Did participant receive care from another health care facility at any time during the study? | | | | | | | |
|  Yes,  *list names and date of first attendance* | F1a. Facility name | |  | | F1b. Date first received services | - -  DAY(*dd*) MONTH (mmm) YEAR **(yy)** | |
| F1c. Facility name | |  | | F1d. Date first received services | - -  DAY(*dd*) MONTH (mmm) YEAR **(yy)** | |
| F1e. Facility name | |  | | F1f. Date first received services | - -  DAY(*dd*) MONTH (mmm) YEAR **(yy)** | |
| ** Collect visit history from transfer clinics using VISIT HISTORY FORM** | | | | | | |
|  No | ** END** | | | | | | |

| **SECTION F: TRACKER FEEDBACK** | | | | | | | | | |
| --- | --- | --- | --- | --- | --- | --- | --- | --- | --- |
| F1. How many persons were questioned by phone or in person while looking for this patient? | | | | |  |  | | --- | --- | | | F2. How many hours were spent by phone or in person looking for this patient? | | : | |
| Hours *(hh)* : Minutes *(mm*) | |
| F2b. How many trips were made looking for this patient? | | | |  |  | | --- | --- | |  Not applicable, phone tracking only | | | | | |
| F3. Does patient have a new site or residence? | | |  Yes: Address known  *Update contact form*   Yes: He/she has moved but do not know where   No   Don’t Know  Not applicable (died) | | | | F4. Does the patient have a new phone contact number? | |  Yes: *Update contact form*   No   Don’t Know   Not applicable (died) |

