| **Skip to F6 if patient or key informant interviewed.** “Site” refers to smallest geographic unit available to tracker in clinic records. “Residence” is the actual building or dwelling where the patient stays or has stayed. | | | | | | | | | |
| F5. What was the tracking outcome? | | | | | | | | | |
|  Site found and residence found | ****F5a. Why was no further information about the patient obtained? | | | |  No one available to speak to   None of the available persons were willing to talk   None of the available persons knew the patient   No one willing to talk about the patient even though they know him/her   No one knows the patient’s current vital status or care status even though they know him/her   Other, specify: | | | | |
|  Site found but residence not found | ****F5b. Why were you unable to find the residence? | | | |  Site refers to an area that is too big to be able to narrow search for patient   No one available to speak to   None of the available persons was willing to talk   None of the available persons knew the patient   No one willing to talk about residence even though they know him/her   No one knows about residence even though they know him/her   Other, specify: | | | | |
|  Site not found and therefore residence of patient was not found | ****F5c. Why were you unable to find the site given by the clinic? | | | |  Site does not exist   Site inaccessible (e.g.,flood)   Site data not legible enough to understand   Other, specify: | | | | |
|  Phone tracking only; no geographic information available for tracking | ****F5d. Why was phone tracking unsuccessful? | | | |  The phone number is invalid   No one answered the phone   The person answering the phone does not know the patient   The person answering the phone refused to provide information about the patient   Other, specify: | | | | |
| F6. Describe any unusual events that took place during the tracking | |  | | | | | | | |
| F7. Describe any “lessons learned” in tracking this patient. | |  | | | | | | | |

| Kanyakla Study  Date of Interview: //  Day Month Year | | | | | | | Participant ID: Interviewer Initials: | |
| --- | --- | --- | --- | --- | --- | --- | --- | --- |
| **SECTION A. ADMINISTRATIVE [TO BE COMPLETED FROM CLINIC DATA]** | | | | | | | | |
| A1. At study closure, was patient actively in care at original clinic? | | | | |  Yes   No ** complete LTFU form** | | | |

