| **SECTION B. MISSED VISITS**  ***Only for patients who miss a visit by 30-days and then come back to the same clinic. All other types of care gap will be addressed by LTFU form.*** | | | | | | | | |
| B1. During the past 12 months, did you receive more than 2-weeks supply of HIV medications from any source other than your regular clinic? | | | | | | | | |
|  Yes | B1a. What sources did you receive medication from? | | | B1b. What months did you receive medication from each of these sources? | | | | B1c. What type of medication? *(check all that apply)* |
|  Another clinic, name: | | |  | | | |  CTX   ARVs |
|  Family/friends | | |  | | | |  CTX   ARVs |
|  Other, specify: | | |  | | | |  CTX   ARVs |
| ** For any additional clinics patient visited, collect visit history from transfer clinics using VISIT HISTORY FORM** | | | | | | | |
|  No | ** go to SECTION C** | | | | | | | |
| **SECTION C. DISCLOSURE** | | | | | | | | |
| C1. Not counting healthcare workers, have you disclosed your HIV status to anyone? | | | | | | | | |
|  Yes | | C1a. Not counting healthcare workers, how many people have you disclosed your status to? | | | | C1b. Which groups of people have you disclosed to?  (check all that apply) | | |
| Number of people |  Too many to count   Refuse to answer | | | 1  Sexual partner  2  Other family  3  Friends  4  Coworkers  5  Members of a group (e.g. support group, church, etc)  6  Other, specify: | | |
|  No | | ** skip to SECTION D** | | | | | | |

| **SECTION D. HIV-RELATED STIGMA** | | | | | |
| --- | --- | --- | --- | --- | --- |
| **How do you feel about being HIV positive?** | **Strongly disagree** | **Disagree** | **Neutral** | **Agree** | **Strongly Agree** |
| D1. Having HIV makes me feel like I’m a bad person |  |  |  |  |  |
| D2. I feel I’m not as good as others because I have HIV |  |  |  |  |  |
| D3. I feel ashamed of having HIV |  |  |  |  |  |
| D4. I think less of myself because I have HIV |  |  |  |  |  |
| D5. Having HIV makes me feel unclean |  |  |  |  |  |
| D6. Having HIV is disgusting to me |  |  |  |  |  |
| **How likely is it that people will treat you in the following ways in the future because of your HIV status?** | **Very unlikely** | **Unlikely** | **Neither unlikely nor likely** | **Likely** | **Very likely** |
| D7. Family members will avoid me |  |  |  |  |  |
| D8. Family members will look down on me |  |  |  |  |  |

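### The end-of-study question on medication from other sources looks back only 12 months, although follow-up runs 12 to 18 months, so for early enrollees who had a gap and returned it does not reach back to enrolment

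*Protocol*

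**What the plan says.** **End-of-study survey (Protocol, Appendix G).** Section B is restricted: "Only for patients who miss a visit by 30-days and then come back to the same clinic". The heading goes on: "All other types of care gap will be addressed by LTFU form". Item B1 then asks: "During the past 12 months, did you receive more than 2-weeks supply of HIV medications from any source other than your regular clinic". A yes leads to collection of the visit history from any additional clinic named.

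**LTFU tracing form (Appendix F).** It asks: "Did participant receive care from another health care facility at any time during the study". There is no 12-month limit. Two places say who gets this form. Appendix G, item A1 asks "At study closure, was patient actively in care at original clinic" and sends a no to the LTFU form. Measurements requires the tracing survey for participants who transferred out or who "missed a clinic visit by ≥90 days and did not return to clinic".

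**Timing.** Measurements places the closing survey at study closure. Research Questions, hypothesis 4, fixes retention "as of study closure at 12 months post-enrollment of the last study participant". Data Analysis, Hypothesis 4, words closure as 12 months after study enrolment and does not mention the last participant. Time Frame puts enrolment in months 3-8 and follow-up in months 9-20, with at least 12 months for each participant.

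**Outcomes.** Hypothesis 1 concerns 90-day absence over the 12 months after randomization. For Hypothesis 2, days out of care are obtained by "summing the total number of days between missed appointments and next clinic visits" over follow-up. The Abstract lists both outcomes as primary.

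**The concern.** Both primary outcomes are built from visit histories. A participant who misses appointments at the original clinic but collects medication at a facility outside the study is in care. The record shows this only if someone learns of that facility and obtains its visit history. For a participant who is back at the original clinic by closure, B1 is the survey item designed to bring such care to light.

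B1's window is counted back from the interview, whereas the outcome window is counted forward from enrolment. If closure is a common date, the two windows coincide only for the last participant enrolled. For the first enrolled, the first half of the outcome year goes unasked. The tracing form serves the same purpose and asks about the whole study, and the protocol gives no reason for the difference.

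At stake is misclassification of time in care and, for a long spell, of 90-day absence. Analysis cannot recover a facility that the participant was never asked to name.

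**Working it through.** **Inputs.** Enrolment runs from the start of month 3 to the end of month 8, and follow-up ends at the end of month 20 (Time Frame). Closure is common, 12 months after the last enrolment (Research Questions). B1 looks back 12 months (Appendix G). Uniform enrolment is an assumption.

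**Step 1: the plan's own figure.** Measure time in months from the start of the project, so that enrolment time *e* runs from 2 to 8 and closure is at 20. Follow-up = 20 − *e*. For the last enrolled this is 20 − 8 = 12 months, which reproduces the stated minimum of 12. For the first enrolled it is 20 − 2 = 18 months.

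**Step 2: time that B1 does not ask about.** Unasked time = follow-up − 12 = 8 − *e*.

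| Enrolled at | Follow-up (months) | Unasked (months) | Share of follow-up | Share of first 12 months |
|---|---|---|---|---|
| start of month 3 (*e* = 2) | 18 | 6 | 33% | 50% |
| mid-period (*e* = 5) | 15 | 3 | 20% | 25% |
| end of month 8 (*e* = 8) | 12 | 0 | 0% | 0% |

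Under uniform enrolment, unasked time is uniform on 0 to 6 months. Its mean is 3 months: 3/12 = 25% of the outcome year, or 3/15 = 20% of mean follow-up. Unasked time always lies at the start of follow-up and never exceeds 6 months, so all of it falls inside the 12-month window.

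**Step 3: the other reading of closure.** If closure is each participant's own 12-month date, as Data Analysis, Hypothesis 4 can be read, follow-up is 12 months and unasked time is 12 − 12 = 0.

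**Step 4: does the LTFU form fill the hole?** Take a participant who had a gap of 30 days or more, used an outside facility, and is active at the original clinic at closure.
- Appendix G, item A1: the answer is yes, so the LTFU form is not triggered.
- Measurements, lost: the definition requires that the participant did not return. This one did.
- Measurements, transferred out: met only if the temporary move was recorded as a transfer.

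The whole-study question therefore does not clearly reach this participant. The same triggers leave the routing of gaps under 30 days unclear, although Section B assigns all other gaps to the LTFU form.

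**Step 5: effect on one affected participant.** An uncaptured 90-day spell lowers time in care by 90/365 = 25 percentage points over 12 months, or 90/548 = 16 points over 18 months, and could also count as a 90-day absence. A 29-day spell lowers it by 29/365 = 8 or 29/548 = 5 points.

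These are effects per affected person. The document does not say how many there are, so no effect on the arm contrast can be computed.

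**The case against.** The strongest reply is that B1 is one item in a larger capture system. Study Design Overview takes full visit histories at all included study clinics, follows official and unofficial transfers within Nyanza to the new facility, and traces participants lost during the study. Measurements repeats the transfer follow-up and commits to clinic data from other clinics used during the study. None of these routes has a 12-month limit. Someone absent for 90 days meets the definition of lost before returning and may be traced while away, and the tracing form itself provides for people found back at their original clinic. **This stands.** A reader might infer that care elsewhere in the early months is, as a rule, counted as time out of care. The document does not support that. The exposed group is limited to returners who used a non-study source that was neither recorded as a transfer nor found by tracing.

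Three further inferences also fail:
- *That gaps under 30 days are never checked.* Section B assigns other gaps to the LTFU form. What can be shown is a conflict between that statement and the form's triggers.
- *That a quarter of person-time is misclassified.* The 25% is time outside one item's recall. Misclassification also needs a gap, outside care, a return and no other record of that care.
- *That the error favours one arm.* The item is the same in both arms, and nothing in the text gives a direction.

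The reply that closure may be per participant stands in part. The wording in Data Analysis allows it and would bring the loss to zero, but Research Questions and Time Frame both point to a common date.

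What the objection does not answer is why the two forms use different windows, or which form picks up a returner's early care if nobody recorded a transfer.

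**Conclusion.** The point holds in limited form. Under the common closure date in Research Questions and Time Frame, B1 misses between 0 and 6 months at the start of follow-up for participants who had a gap of 30 days or more and returned. The mean is 3 months if enrolment is uniform. The whole-study question on the LTFU form does not clearly reach these participants. Outside care in that period that no other route records can be scored as out of care, and a long spell as a 90-day absence.

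The conclusion rests on closure being a common date; under per-participant closure the recall gap disappears. The number of participants affected, and hence the effect on either primary comparison, cannot be derived from the document. This is a cheap improvement to a form and is no evidence that the primary outcomes are materially wrong.

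**What to change.** 1. Reword B1 to begin 'Since you joined the study on [enrolment date]', with the date filled in beforehand. This matches the LTFU form's whole-study window, is correct under either reading of closure, and brings the unasked period to zero for everyone who is asked Section B.
2. Reconcile the closure definitions in Research Questions (hypothesis 4) and Data Analysis (Hypothesis 4).
3. Reconcile Section B's statement that other gaps go to the LTFU form with that form's triggers in Measurements and Appendix G, item A1, so that each gap counted under Hypothesis 2 is routed to one of the two forms. Whether very short gaps merit an interview question is a trade-off: asking up to 18 months later about lapses of a few days adds recall error. The routing should be stated either way.

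The cost is one reworded item and some clarified text before the closing survey is fielded, slightly longer recall for early enrollees, and a few more record look-ups at other facilities.

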**Session**

**6**

**Session 1**

**Session**

**2**

**Session 4**

**HIV on Lake Victoria:**

**Biology and**

**Sociology**

**Combination Antiretroviral**

**Therapy (cART):**

**How and Why**

**ARV’s and You:**

**Nutrition and Herbal Medication**

**Chasing Stigma:**

**Group Support and**

**Communication**

**Engaging with Care:**

**Being an Active**

**Patient**

**Session**

**3**

**Session**

**5**

**Pulling the**

**Net Together:**

**Counseling and Confidentiality**

*

****Facilitated**

**Group VCT Session**

**(Optional)**

**Session 1: HIV on Lake Victoria**

| **Topic** | **Method** | **Min** | **Content Summary** |
| --- | --- | --- | --- |
| Prayer and Introductions | class | 5 | - Have opening prayer. - Introduce members/facilitators |
| The Kanyakla | Class | 15 | - Discuss the MHN Kanyakla Program Goals and Overview |
| Daily Meditations | class | 15 | - Refer to daily meditation sheet. |
| Knowns and Unknowns | teaching game | 15 | - Listing what the group “knows” about HIV - List group “unknowns” |
| HIV on Lake Victoria | discussion | 10 | - Discuss local HIV stats and facts using KAIS 2013 |
| HIV games | teaching games | 35 | 1. HIV body game 2. HIV hidden ball game 3. HIV Fluids game |
| HIV biology | discussion | 30 | - Overview of HIV/AIDS |
| Wisdom Circle | class | 10 | - Review Handout |
|  | Total time | 135 Minutes | |

